#### HHCs screening positive for TB symptoms and/or with a dCXR suggestive of TB

HHCs screening positive for symptoms and/or those with dCXRs suggestive of TB are asked for a sputum sample, which is investigated using Xpert MTB/RIF Ultra (Cepheid). If this sample is positive for *Mtb* (including a trace result), a minimum of two additional sputum samples are investigated, following decontamination, with Xpert MTB/RIF Ultra, solid and liquid culture. Isolates stored from these cultures will be sequenced for matching with the IC isolates in order to verify intrahousehold transmission. Sputum induction is performed for those unable to provide a spontaneous sputum sample. HHCs with microbiologically confirmed TB are referred for TB treatment to the National TB Programme.

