**Methods and analysis:**

A total of 2100 HHCs (aged ≥10 years) of adults with microbiologically-confirmed pulmonary TB will be recruited and followed up at 6-month intervals for 18–24 months. At each time point, a WHO symptom screen and digital chest radiograph (dCXR) will be performed, and blood and urine samples will be collected. Individuals screening positive (WHO symptom screen or dCXR) will be requested to provide sputum for Xpert MTB/Rif Ultra. At baseline, HHCs will also be screened for HIV, diabetes (HbA1c), chronic lung disease (spirometry), hypertension and anaemia. Study outcomes will be coprevalent TB (diagnosed at enrolment), incident TB (diagnosed during follow-up) or no TB at completion of follow-up. Novel diagnostics will be validated using fresh and biobanked samples with a nested case–control design. Cases are defined as HHCs diagnosed with TB (for early diagnosis) or with incident TB (for prediction of progression) and will be matched by age, sex and country to HHCs who remain healthy (controls). Statistical analyses will include assessment of diagnostic accuracy by constructing receiver operating curves and calculation of sensitivity and specificity.

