**Figure 3 F3:**
[figure not shown]
Eligibility criteria and schedules of events for index cases and household contacts. A=depending on the time point of study enrolment and consequently on the duration available for follow-up, that is, 18 or 24 months, the follow-up visit at 24 months±30 days may be conditional; B=the follow-up visit by phone may be conducted after the last scheduled follow-up visit at 18 months±30 days or 24 months ±30 days to assess whether symptoms suggestive of TB have occurred, TB diagnosis has been made or anti-TB treatment has been initiated; C=unwell visits by phone or on-site may be conducted between scheduled follow-up visits if a participant presents at a recruitment healthcare facility with signs and symptoms suggestive of TB; D=coached spontaneous or induced sputum collection for storage at scheduled follow-up visit at 18 months±30 days or 24 months ±30 days, and for repetition of HIV testing if tested negative at baseline; E=coached spontaneous or induced sputum collection on the decision of the investigating team for testing by Xpert MTB/RIF Ultra if participant presents with signs and symptoms suggestive of TB; F=coached spontaneous or induced sputum collection in case of Xpert MTB/RIF Ultra positivity or strong clinical suspicion of TB for repetition of the Xpert MTB/RIF Ultra; G=in case of HIV positivity to be followed by the assessment of CD4 counts; H=CXR to be conducted at an unscheduled on-site unwell visit on the decision of the investigating team depending on the nature of symptoms reported, and the time elapsed since the last CXR including its findings; I=not to be conducted among pregnant women; J=stored venous blood includes 6 mL EDTA blood for whole blood and plasma, 4 mL serum and 2.5 mL PAXgene blood, all samples will be deep frozen for retrospective testing using new diagnostics as described in text; K=in case the evaluation of symptoms of a participant unable to present at a recruitment healthcare facility is required an unscheduled on-site or home visit will be arranged by phone, the resolution of symptoms can alternatively be addressed by phone; L=collection of PBMC at baseline and follow-up visit at 6 months±30 days is optional, thus will not be performed at each participating site and for each participant; M=in case the evaluation of symptoms of a participant unable to present at a recruitment healthcare facility is required or doubtful if required an unscheduled unwell visit by phone will be arranged, the resolution of symptoms can alternatively be addressed by phone; N=spirometry and/or diabetes (HbA1c) will be performed at scheduled follow-up visits at 6 months±30 days, 12 months ±30 days and 18 or 24 months±30 days if required or not performed at baseline, anaemia (Hb) will be performed at baseline and scheduled follow-up visits at 6 months±30 days, 12 months ±30 days and 18 or 24 months±30 days if possible; O=blood pressure measurement will be performed at baseline and scheduled follow-up visits at 6 months±30 days, 12 months ±30 days and 18 or 24 months±30 days; P=WGS to be performed once *Mtb* infection is confirmed and an isolate could be recovered. CD4, cluster of differentiation 4; CXR, chest radiograph; Hb, haemoglobin; HbA1c, glycated haemoglobin; IGRA, interferon gamma release assay; LAM, lioparabinomannan; MTB, *Mycobacterium tuberculosis*; MBLA, molecular bacterial load assay; PBMC, peripheral blood mononuclear cell; RIF, rifampicin; TAM-TB, T- cell activation marker tuberculosis; TB, tuberculosis; WGS, whole genome sequencing.

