#### Household contacts

Informed consent is obtained from all eligible adult HHCs. For HHC <18 years of age, the guardian is asked to provide informed consent, with assent also sought from children dependent on local guidance. At baseline, a questionnaire is administered collecting information on socioeconomic and demographic characteristics, previous medical history of TB, HIV and other diseases, exposure risk factors, smoking and alcohol history. The physical examination includes height, weight, mid-upper arm circumference and blood pressure measurement. In addition, all HHCs are offered free HIV testing according to the National Guidelines. All people with confirmed HIV infection will have CD4 counts performed and be referred for TB preventive therapy. Those not yet on antiretroviral therapy (ART) and those who interrupted ART are referred for ART at local services.

Point of care HbA1c (A1cCare, SD Biosensor, Gyeonggi-do, Republic of Korea) and haemoglobin (Hemocue 301+, Hemocue, Angelholm, Sweden) tests and spirometry (including prebronchodilation and postbronchodilation with inhaled salbutamol) are performed at baseline or the 6-month visit. HHCs who did not take up HIV testing or other screening at baseline are offered these tests at each study visit. Any HHCs with test results requiring treatment or further investigations are referred for respective services.

HHCs are screened for TB using the WHO symptom screening questionnaire and a dCXR, reviewed by a clinical officer. dCXRs are not performed in pregnant HHCs. HHCs with a positive WHO symptom screening and/or abnormal dCXR are asked to provide sputum samples for TB investigations, that is, for GeneXpert and mycobacterial culture. Those with negative symptom screen and normal dCXR are asked to provide a spontaneous sputum sample for storage (with sputum induction performed if required).

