### Novel test candidates

A range of novel test candidates targeted at pathogen detection or identification of host responses to *Mtb* are being applied, either in real-time (for all participants) or retrospectively (in a case–control design). While a number of novel test candidates have been prespecified, the ERASE-TB biobanking processes allow for addition of further candidate tests to be evaluated on stored samples as they become available.

DCXRs offer good sensitivity for diagnosis of pulmonary TB. However, high interinvestigator and intrainvestigator variability, and lack of trained interpreters presents a barrier to implementation in many high-TB burden settings. Computer-aided interpretation systems, such as CAD4TB (Delft Imaging, Hertogenbosch, Netherlands) and qXR (Qure.ai, India), may increase image-reading capacity, with good performance, and serve, therefore, as a systematic screening tool to identify individuals in need of confirmatory TB tests.^17 18^

Xpert MTB/RIF Ultra is a nucleic acid amplification test for *Mtb* with a lower limit of detection compared with the previous Xpert MTB/RIF generation, and, therefore, conferring higher sensitivity in paucibacillary specimens. This, however, comes at the expense of specificity, particularly in high TB incidence settings, resulting in ‘false positives’.^19^ WHO guidelines recommend Xpert MTB/RIF Ultra for TB diagnosis among adults and children acknowledging that further evaluation, particularly of the role of Xpert MTB/RIF Ultra for TB screening, is needed.^20 21^

FLOW-TB is an advanced ELISA for the detection of *Mtb* lipoarabinomannan (a mycobacterial cell wall component) in urinary specimens with results available within 65 min.^22^

The TAM-TB detects Mtb-specific CD4 T-cells through in vitro antigen stimulation with *Mtb*-derived peptides, that is, from ESAT-6 to CFP-10, followed by flow cytometry. TAM-TB discriminated latent *Mtb* infection from TB in freshly collected blood with 83% sensitivity and 96%–98% specificity in previous studies. Furthermore, TAM-TB may detect early TB disease progression up to 9 months prior to the identification of *Mtb* in sputum.^23–25^

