### Statistical analyses

Baseline characteristics and analytical data will be summarised using descriptive statistics inclusive of mean, median, range, SD and absolute as well as relative frequencies depending on the nature of data. A logistic regression model will be used to identify characteristics of TB among ICs, households and HHCs that are predictive of incident TB. From the study database, we will simulate algorithms of different tests to obtain the testing combination with the best accuracy. We will couple tests with a mathematical model that quantifies the risk of infection and/or disease to enhance predictive performance. The reporting of the development of the prediction model will follow the Transparent Reporting of a multivariable prediction model for Individual Prognosis Or Diagnosis Initiative.^38^

The validation of novel diagnostic tests for detecting TB will be analysed as a 1:4 matched nested case–control study with HHCs diagnosed with TB at baseline and during follow-up serving as cases, and HHCs who do not develop TB during follow-up as controls; controls will be matched for site, age, sex, HIV status and other risk factors for developing TB. Sensitivity and specificity of novel tests will be determined using pre-existing positive/negative cut-offs where these exist^39^; and receiver operating curves (ROC) constructed with area under the ROC curve calculated. For tests aiming to identify individuals at high risk of TB in the future, only HHCs who are diagnosed with TB during follow-up will serve as cases (ie, those diagnosed with TB at baseline will be excluded). Stored samples from all timepoints will be retrieved and diagnostic accuracy (ie, sensitivity and specificity) of the novel test determined at different timepoints before TB diagnosis. The decision of assigning the ‘active TB’ endpoints to participants will be blinded from the new test results to avoid inclusion bias.

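### Xpert Ultra is both a candidate test and part of the TB endpoint work-up, two sections conflict on culture after a negative Ultra, and the blinding statement cannot hold for it

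*Protocol article*

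**What the plan says.** All references are to the Protocol article.

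- *Study objectives*: the first primary objective is the sensitivity and specificity of novel diagnostics, with emphasis on TB with few or no symptoms.
- *Novel test candidates*: Xpert Ultra is one of the tests described, and the section reports WHO guidance acknowledging that "further evaluation, particularly of the role of Xpert MTB/RIF Ultra for TB screening, is needed". Computer-aided reading of the digital chest radiograph (dCXR) is also listed.
- *Household contacts*: contacts with a positive symptom screen and/or abnormal dCXR "are asked to provide sputum samples for TB investigations, that is, for GeneXpert and mycobacterial culture". No Ultra result is required first. Screen-negative contacts "are asked to provide a spontaneous sputum sample for storage".
- *HHCs screening positive for TB symptoms and/or with a dCXR suggestive of TB*: the first sputum sample goes to Ultra. If it is positive, trace included, "a minimum of two additional sputum samples are investigated, following decontamination, with Xpert MTB/RIF Ultra, solid and liquid culture". Culture after a negative first Ultra is not mentioned.
- Abstract, *Methods and analysis*: screen-positives "will be requested to provide sputum for Xpert MTB/Rif Ultra". Culture is not mentioned.
- Figure 3 legend, note F: further sputum "in case of Xpert MTB/RIF Ultra positivity or strong clinical suspicion of TB for repetition of the Xpert MTB/RIF Ultra". Note E leaves sputum for Ultra in symptomatic participants to the investigating team.
- *Study endpoints*: a committee reviews the data and the case classification.
- *Statistical analyses*: endpoint assignment "will be blinded from the new test results to avoid inclusion bias". No exception is made for Ultra.

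**The concern.** A test's sensitivity can be estimated only among cases that were identified without its help. If a positive Ultra is the way into the microbiological work-up, contacts with TB but a negative Ultra do not reach the case set at that visit. Ultra's false negatives are then unobservable and its sensitivity is no longer an empirical result. If culture is done whatever Ultra shows, the false negatives can be seen, but a reference that counts Ultra positivity as evidence of TB still favours Ultra.

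The effect reaches the other candidates too. With culture conditional on Ultra, they are judged on Ultra-detected TB, while early disease with few bacilli is what the first objective is most interested in. A contact missed at baseline may later be counted as incident, or may finish as TB-free.

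The blinding sentence presents endpoint assignment as independent of the tests under study. For Ultra it is not.

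**Working it through.** **1. The two sections side by side**

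| Contact | *Household contacts* | *HHCs screening positive…* |
|---|---|---|
| Screen-positive, first Ultra positive | culture | culture |
| Screen-positive, first Ultra negative | culture | no culture stated |

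They differ only in the second row, and that row decides whether Ultra can be seen to miss a case. The abstract agrees with the right-hand column. Note F adds a route for an Ultra-negative contact, but to a repeat Ultra, not to culture.

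**2. Blinding**

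Ultra is a listed candidate, and its result is part of the microbiology used to find cases in both columns. Endpoint assignment therefore cannot be blind to it under either reading.

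**3. The plan's own figures**

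*Sample size* gives 15 coprevalent + 49 incident = 64 cases, and 64/2100 = 3.05%, stated as 3%. Controls for the incident cases are 49 × 4 = 196. The stated confidence intervals also reproduce as exact 95% limits: 36/49 gives 58.9–85.1%, 40/49 gives 68.0–91.2%, 180/196 gives 87.1–95.3% and 184/196 gives 89.6–96.8%. None of this is in dispute.

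**4. Size of the effect**

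Two inputs are not in the document and are assumed:

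- s, the true sensitivity of a first Ultra in screen-positive contacts with TB: 60% to 90%.
- r, the share of first-Ultra-negative TB that still enters the case set: 0 (strict gate) to 1 (all found by culture).

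The 64 are taken as cases found, because *Sample size* describes them as diagnosed.

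- Apparent first-Ultra sensitivity = s / (s + (1 − s)r)
- Cases missed per 64 found = 64 / (s + (1 − s)r) − 64

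At r = 0 the first formula is s/s = 100% for every s. The estimate would be 64/64, with an exact 95% interval of 94.4–100% that says nothing about s. The second formula becomes 64/s − 64; for example, 64/0.6 − 64 = 42.7.

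| s | Missed, r = 0 | Missed, r = 0.5 | Apparent, r = 0 | Apparent, r = 0.5 | Apparent, r = 1 |
|---|---|---|---|---|---|
| 60% | 42.7 | 16.0 | 100% | 75.0% | 60% |
| 70% | 27.4 | 11.3 | 100% | 82.4% | 70% |
| 80% | 16.0 | 7.1 | 100% | 88.9% | 80% |
| 90% | 7.1 | 3.4 | 100% | 94.7% | 90% |

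At r = 1 none is missed among screen-positives who give sputum.

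The apparent-sensitivity columns count a recovered case as a first-Ultra negative. A contact recovered because Ultra turns positive at a later visit lowers the missed count, but is Ultra-positive at the visit that makes the diagnosis. That kind of recovery leaves diagnostic-visit sensitivity at about 100%.

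**5. Computer-aided dCXR**

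At scheduled visits, sputum testing follows symptoms or a clinical officer's reading of the film. If symptoms are absent and the officer calls the film normal, sputum is stored even if the software would have flagged the image. Verification is therefore partial for the software. This is a lesser and separate matter.

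**The case against.** The strongest reply is that nothing is settled until it is known which section governs. If every screen-positive contact is cultured, as *Household contacts* says, Ultra-negative, culture-positive contacts become cases and sensitivity can fall to its true value. This stands, and it is why the 100% figure is conditional. The *Household contacts* sentence could also be a loose summary of the later section. The conflict would then be one of wording only, but the gate would stand in full.

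A reader might infer that nobody becomes a case without a positive Ultra, or that symptoms and dCXR are the only routes to a sputum test. The document does not support either. It gives no full case definition, which an article may leave to the full protocol, and it has a review committee. Notes E and F add clinical judgement as a route to sputum.

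A reader might also take the 43 to 7 cases as never identified. That goes too far: contacts are rescreened every 6 months, unwell visits are possible and Ultra may be repeated, so some would surface later.

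Ultra run on sputum stored at earlier visits is not affected by construction. *Statistical analyses* names no Ultra-specific analysis, and Ultra is one of many candidates.

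The blinding sentence may have been meant only for tests outside the diagnostic work-up. As written it makes no such exception.

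For computer-aided dCXR, it would be wrong to say that the software is judged against itself. The trigger is the officer's reading, and symptoms alone also suffice.

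**Conclusion.** The point holds in conditional form. Three things are in the text and need no assumption: Ultra is both a candidate and part of the endpoint work-up, two sections conflict on culture after a negative Ultra, and the blinding statement cannot be true of Ultra.

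The consequence depends on which section governs. If culture requires a positive Ultra, diagnostic-visit sensitivity is about 100% whatever the truth, and Ultra-negative, culture-positive disease is left out of the case set at that visit. At most 43 cases (s = 60%) down to 7 (s = 90%) would be missed per 64 found. This is an upper bound: it uses an assumed range for s and allows no recovery. With half recovered, it falls to 16 down to 3. If culture is unconditional, only part of the incorporation bias remains.

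The document does not support a flat statement that Ultra's sensitivity is 100% by construction or that such disease is lost for good.

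**What to change.** 1. Reconcile *Household contacts* with *HHCs screening positive…* (and the abstract), so that one rule states whether culture depends on the Ultra result, and record what sites have done so far.
2. Where culture is done regardless of Ultra, report Ultra's accuracy against a culture-only reference.
3. Where culture is conditional on Ultra, do not report diagnostic-visit Ultra sensitivity as an accuracy result. State that the case set for the other tests is limited to Ultra-detected TB.
4. In *Statistical analyses*, limit the blinding sentence to tests that play no part in the endpoint.
5. As a lesser item, describe computer-aided dCXR accuracy as subject to partial verification through symptoms and the officer's reading.

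The cost is mostly wording and a narrower claim for Ultra. There is more culture work only if sites now culture solely after a positive Ultra and the reconciled rule extends it. Recruitment began in 2021, so visits already completed may not be recoverable; for those, items 3 and 4 are the practical remedy.

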### Patient and public involvement

The ERASE-TB study sites have established Community Advisory Boards, which are voices of communities, people affected and study participants, providing a strategic link between the communities and the study team. Community Advisory Boards meet regularly and provide feedback on design, procedures and conduct of the study. They will also be closely involved in the dissemination of study results. In addition to the Community Advisory Boards, each study site conducts community engagement activities focused on young people with the aim to foster interst in science and research, specifically in the field of respiratory diseases/illness. This includes close partnership with schools and universities. Furthermore, planned qualitative research will specifically aim to understand the perceptions of HHCs with regards to TB diagnostics and screening.

### Sample size

An estimated 800 to 900 TB-confirmed ICs are required for the subsequent enrolment of an anticipated 2100 HHCs, that is, 700 HHCs per country. Loss to follow-up of HHCs is estimated to be 10%. A total of 64 HHCs (3%) are estimated to be diagnosed with TB during the study period, based on previous active case finding studies among HHCs.^16^ Validation for subclinical and early TB will include incident (n=49) and coprevalent TB cases (n=15). Validation for detection of incipient *Mtb* infection will include samples of participants with incident TB (n=49) matched 1:4 to samples of participants without TB (n=196). For tests diagnosing incipient *Mtb* infection sensitivities of 73% and 82% would be detected with a precision of 59%–85% and 68%–91%, respectively. For specificities of 92% and 94%, the CIs would be 87% to 95% and 90% to 97%.

### Novel test candidates

A range of novel test candidates targeted at pathogen detection or identification of host responses to *Mtb* are being applied, either in real-time (for all participants) or retrospectively (in a case–control design). While a number of novel test candidates have been prespecified, the ERASE-TB biobanking processes allow for addition of further candidate tests to be evaluated on stored samples as they become available.

DCXRs offer good sensitivity for diagnosis of pulmonary TB. However, high interinvestigator and intrainvestigator variability, and lack of trained interpreters presents a barrier to implementation in many high-TB burden settings. Computer-aided interpretation systems, such as CAD4TB (Delft Imaging, Hertogenbosch, Netherlands) and qXR (Qure.ai, India), may increase image-reading capacity, with good performance, and serve, therefore, as a systematic screening tool to identify individuals in need of confirmatory TB tests.^17 18^

Xpert MTB/RIF Ultra is a nucleic acid amplification test for *Mtb* with a lower limit of detection compared with the previous Xpert MTB/RIF generation, and, therefore, conferring higher sensitivity in paucibacillary specimens. This, however, comes at the expense of specificity, particularly in high TB incidence settings, resulting in ‘false positives’.^19^ WHO guidelines recommend Xpert MTB/RIF Ultra for TB diagnosis among adults and children acknowledging that further evaluation, particularly of the role of Xpert MTB/RIF Ultra for TB screening, is needed.^20 21^

FLOW-TB is an advanced ELISA for the detection of *Mtb* lipoarabinomannan (a mycobacterial cell wall component) in urinary specimens with results available within 65 min.^22^

The TAM-TB detects Mtb-specific CD4 T-cells through in vitro antigen stimulation with *Mtb*-derived peptides, that is, from ESAT-6 to CFP-10, followed by flow cytometry. TAM-TB discriminated latent *Mtb* infection from TB in freshly collected blood with 83% sensitivity and 96%–98% specificity in previous studies. Furthermore, TAM-TB may detect early TB disease progression up to 9 months prior to the identification of *Mtb* in sputum.^23–25^

Multiple transcriptomic signatures, capturing the host response to TB, have been described as promising candidate tests for earlier TB diagnosis (up to 2 years before microbiological diagnosis). An individual patient data meta-analysis suggested equivalent performance of eight signatures, with 25%–40% sensitivity and 92%–95% specificity, 0–24 months before TB diagnosis. Diagnostic accuracy of each signature improved as the interval between testing and microbiological TB diagnosis shortened.^26^ Several signatures have been developed into PCR-based assays to facilitate real-time implementation: the recent The Correlate of Risk Targeted Intervention Study (CORTIS) reported sensitivity of 48% and specificity of 75% for incipient TB for the RISK-11 transcriptomic signature of TB risk.^27^ Cepheid have developed a three-transcript TB score into a fully automated in-cartridge PCR assay performed on finger-prick blood using the Xpert platform (Xpert TB Host Response RUO Prototype cartridge). This cartridge will be evaluated using freshly collected specimens in ERASE-TB; storage of RNA-stabilised blood samples also allows for retrospective evaluation of additional transcriptomic signatures in our cohort.^28 29^

An alternative approach to capture the host response to TB is through protein-based biomarker signatures. Candidate tests in this category include a serum-based or plasma-based multiplex assay assessing 13 protein biomarkers (C reactive protein, procalcitonin,^30^ sTREM-1 (soluble triggering receptor expressed on myeloid cells-1),^31 32^ angiopoietin-2,^33 34^ IL-6,^35^ TRAIL (TNF-related apoptosis-inducing ligand)^36^ and IP-10^35^) that is being developed by the London School of Hygiene and Tropical Medicine; in addition, a seven biomarker signature is under development as a point-of-care test for TB diagnosis, with 94% sensitivity and 73% specificity detected in previous work.^37^

